#### Secondary clinical outcomes

The proportion of clinical CSOM that fails to improve (determined by perforation size, amount of discharge, time to cessation of discharge) at 4 and 12 months will be analysed in the same manner as the primary clinical outcome described above.

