### Outcome measures

The primary outcome measure was the proportion of children with clinical failure after 16 weeks (4 months) of treatment. Clinical failure was determined by clinical examination for the presence of any ear discharge. Additional secondary outcome measures at 4 months and 12 months included: i) hearing level, determined by audiometry (performed by trained audiologists) and summarised as the pure tone 4 frequency average hearing level at 500, 1000, 2000 and 4000 Hz in the better and worse hearing ears; ii) failure to improve (determined by perforation size and amount of discharge); iii) change in perforation size and amount of discharge (determined by comparison of standardised assessment at baseline with end of study); iv) time to cessation of discharge (determined by review of health records); v) adherence to recommended management including attendance for specialist review (determined by review of health records); vi) presence of recognised bacterial pathogens in nose and ear discharge (determined by standard microbiological culture and antimicrobial sensitivity methods); vii) complications (defined as development of a related illness requiring additional medical treatment); and viii) side effects (defined as development of illness requiring cessation of prescribed treatments). Additional secondary outcomes at 4 months and 12 months from randomisation included the proportion of children with any carriage of pneumococci and any carriage of vaccine or non- vaccine serotype pneumococci and any carriage of NTHi. All children were followed up for any adverse events (AE) and serious adverse events (SAE) by reviewing the child’s clinic and hospital records and asking the parents about any side effects of the treatments between and at visits. We documented any contact the family or child had during the study with the clinic or hospital, including all relevant investigations and treatments. Regular, scheduled home visits, phone calls, SMS texts and social media contact with the families were made and recorded by study nurses or community researchers to support and promote participant retention; and monitor adherence.

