#### Primary clinical outcomes

The primary endpoint is the proportion of children with clinical failure of CSOM after 16 weeks (4 months) of treatment. A binomial regression with logarithmic and identity link will be used to estimate the main effects of the two interventions. Therefore, the relative risk and the risk difference, respectively, with their 95% confidence interval will be reported for the crude and adjusted estimates. The adjustment set will comprise of the stratification factors (age group and community) and the other intervention.

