#### Missing data

The number of participants with primary endpoint and other data available at required timepoints, will be reported. No data imputation for missing data will be carried out. Where reasonable, complete case analysis will apply. All analysis will be two-tailed and statistical significance will be set at *p* < 0.05, using Stata 15.1 (StataCorp, College Station, TX, USA).

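### Failure to improve has two definitions, and the only analysis the article gives for time to cessation of discharge is a proportion

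*Protocol article*

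**What the plan says.** In the protocol article, Outcome measures numbers the secondary outcomes. Outcome ii is "failure to improve (determined by perforation size and amount of discharge". Outcome iv, listed separately, is "time to cessation of discharge (determined by review of health records".

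Secondary clinical outcomes then describes the analysis. It takes the proportion of clinical CSOM that "fails to improve (determined by perforation size, amount of discharge, time to cessation of discharge", and says that this proportion "at 4 and 12 months will be analysed in the same manner as the primary clinical outcome described above". The model referred to is in Primary clinical outcomes: "A binomial regression with logarithmic and identity link will be used to estimate the main effects of the two interventions". It yields a relative risk and a risk difference.

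On incomplete follow-up, Missing data rules out imputation and adds: "Where reasonable, complete case analysis will apply".

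**The concern.** The outcome list and the analysis section do not describe the same endpoint. One builds failure to improve from two components. The other adds a third, which is itself a separate outcome in the list. The analysis section gives no cut-off or combining rule to turn a time into improved or failed, so a child's classification could depend on which section the analyst follows.

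The second issue is the analysis of outcome iv. A time to cessation carries information on how fast ears dry. A proportion at 4 or 12 months keeps only part of it, and a child whose records stop early cannot contribute the time observed until then. If an adjunct mainly shortens the period of discharge, a proportion at a fixed visit may miss much of its effect.

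**Working it through.** **Step 1: the sections side by side**

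| Item | Outcome measures | Secondary clinical outcomes |
|---|---|---|
| Components of failure to improve | perforation size, amount of discharge | perforation size, amount of discharge, time to cessation |
| Time to cessation | own outcome (iv), from health records | component of a binary failure |
| Analysis | none given here | proportion at 4 and 12 months, binomial regression |

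Take a child whose perforation and discharge have both lessened by 4 months. Under the two-component definition the child has improved. Under the three-component version the status also depends on a time criterion that is not stated. The two codings can differ.

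**Step 2: is a time-to-event analysis named elsewhere in the article?**

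Statistical methods names binomial and linear models for subgroups. Carriage outcomes uses binomial regression, Audiology outcomes linear regression and ANCOVA, and Other outcomes a chi-square test. None handles a censored time.

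**Step 3: the plan's own figure**

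The article gives no figure for time to cessation. Its sample size concerns the primary outcome. Inputs from Sample size: failure 70% against 50%, 5% level, 90% power, 10% loss. Missing data states two-tailed tests.

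- n per margin = [1.96 × √(2 × 0.6 × 0.4) + 1.2816 × √(0.7 × 0.3 + 0.5 × 0.5)]² / 0.20² = 124.
- Total = 2 × 124 = 248, and 248 / 0.90 = 276 after rounding up. The stated 280 is consistent.
- With 280 × 0.90 / 2 = 126 per margin, power is 0.905 against the stated 90%.

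The design figure reproduces and does not involve this point.

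**Step 4: how much could a proportion lose?**

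This is an illustration on assumed inputs that are not in the article. There are 126 children per margin, no loss before week 16, and 1000 simulated trials per scenario. The binary analysis is whether discharge had ceased by week 16. The comparator is a log-rank test on week of cessation. Among children who dry, the week is 16 × Beta(s, 1), rounded up, with mean 16 × s/(s + 1) before rounding.

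| Scenario | Ceased by week 16, control v treated | Mean week among those who dry, control v treated | Power, binary | Power, log-rank |
|---|---|---|---|---|
| a: same timing | 30% v 50% | 8.0 v 8.0 (s = 1, 1) | 0.91 | 0.91 |
| b: same proportion, earlier on treatment | 50% v 50% | 10.7 v 5.3 (s = 2, 0.5) | 0.05 | 0.21 |
| c: similar proportion, much earlier on treatment | 80% v 85% | 8.0 v 4.6 (s = 1, 0.4) | 0.19 | 0.89 |

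Check on (a), assuming exponential times: hazard ratio = ln 0.5 / ln 0.7 = 1.94. Events = 126 × (0.3 + 0.5) = 100.8, about 101. Power by Schoenfeld's formula = Φ(√(100.8/4) × ln 1.94 − 1.96) = 0.92, close to the simulated 0.91.

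The loss is nil in (a), modest in (b) and large in (c). The table scores cessation by week 16 only. It is not a simulation of the three-component failure, which cannot be simulated because its combining rule is not stated.

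**The case against.** The strongest reply is that the article condenses a fuller plan. The parenthesis may be a loose list of several secondary outcomes, and a statistical analysis plan that is not shown may give outcome iv a survival model. The article also gives no analysis for adherence (outcome v), so it clearly does not cover everything. This part stands: a missing survival model would not by itself be a finding. It does not remove the conflict, because the article prints both definitions and assigns an analysis to the second. Even as a loose list, the parenthesis gives time to cessation a proportion at two visits.

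A reader might infer more than the text supports:

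- *That a binomial model cannot use children whose discharge never stopped.* It can. They are failures and stay in the denominator.
- *That a duration can never enter a yes/no status.* It can, with a cut-off. The article states none.
- *That the speed of drying will never be estimated, or cannot show in the results.* Outcome iv remains in the list, the proportion is not said to be its only analysis, and a time component in the composite could reflect some of the speed.
- *That partly followed children will certainly be dropped.* Complete-case analysis is planned only where reasonable, so this is likely but not stated.
- *That weekly data are already in hand.* Weekly clinic review belongs to standard treatment (Study design), but outcome iv comes from health records of unstated resolution. Trial status says that some data collection is outstanding.

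**Conclusion.** The point holds as a contradiction within the article about a secondary outcome. Failure to improve has two components in one section and three in another, and the third is a separately listed outcome. The only analysis printed for time to cessation is a proportion at 4 and 12 months, which discards event times and cannot use partial follow-up by censoring.

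The contradiction rests on the text alone and needs no assumption. The size of the information loss does rest on assumptions: the timing of cessation is unknown, and on assumed patterns the loss runs from none to large. The illustration assumes no loss before week 16, so it says nothing about the gain from censoring. The primary outcome, its analysis and the sample size are unaffected.

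**What to change.** 1. In Secondary clinical outcomes, use the two-component definition from Outcome measures (perforation size and amount of discharge) and delete time to cessation from the parenthesis.
2. Analyse outcome iv separately as a time-to-event outcome:
   - time origin: randomisation;
   - event: a stated definition of cessation, the same in all four groups, which says how recurrence is handled, since the Intervention section expects discharge to return in some ears;
   - censoring: at the last available record;
   - model: interval-censored or discrete-time, at whatever resolution the health records support;
   - covariates: both interventions, age group and community, in line with the primary adjustment set.

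The cost is a change of wording and one extra model. The result will depend on how complete the health records are, so their completeness by group should be reported. Trial status says that data cleaning has only commenced, so the change can be fixed before analysis. The primary outcome and sample size stay as they are.

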#### Carriage outcomes

The proportion of children with carriage of any capsular pneumococci, carriage of vaccine serotype capsular pneumococci, non-vaccine serotype capsular pneumococci and any non-typeable *Haemophilus influenzae* (NTHi) *Pseudomonas aeruginosa, Streptococcus pyogenes, Streptococcus aureus, Proteus species* and coliforms at 16 weeks (4 months) and 12 months will be described. A binomial regression will be used to estimate the crude and adjusted effect of the two interventions on carriage outcomes in the same manner as earlier described for the primary clinical outcome.

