## Background

In 2013, remote Indigenous communities participating in ear and nasopharyngeal carriage surveillance found that around 50% of young children (mean age 13 months) had otitis media with effusion (OME), 37% had acute otitis media (AOM without perforation), and 12% had chronic suppurative otitis media (CSOM). [1] CSOM is one of the most significant health problems affecting young Aboriginal children in Australia today [2, 3] having compounding effects on hearing, behaviour and learning. It was not that long ago that children with pus draining from their ears were a common sight in remote communities with more than 50% of young children in some remote communities having long term CSOM. [4, 5] Although the rates of CSOM have decreased, the NT hearing service reported that 53% of young Aboriginal children living in remote NT communities still have some form of hearing loss. [6, 7] Of all forms of ear disease, children diagnosed with CSOM had the highest levels of hearing loss. It should be noted that children with dry perforations and wet perforations (or CSOM) may be interchangeable, depending on the season and the child’s upper respiratory infection status. Combined rates of wet and dry perforation between 2007 and 2011 were 26% (15 and 11%) in 0–5 year olds, 26% (10 and 16%) in 6–11 year olds, and 37% (12 and 25%) in 12+ year olds respectively [7]. While effective timely treatment of acute otitis media with perforation (AOMwiP) aims to prevent CSOM, the challenges involved in delivering appropriate treatment in remote settings mean that a large group of children develop chronic severe ear disease [8]. The early age of onset, the severity of the hearing loss, and the persistence of this infection, means that improving medical management for this condition is a priority. Once CSOM has become established, it is extremely difficult to treat. Ear discharge failed to resolve at the end of topical antibiotic therapy in 70% Indigenous children in our previous randomised trial. [9] While topical antibiotics have been shown to be more effective than oral antibiotics and topical antiseptics, it is unclear whether there are any benefits of combining these treatments [9–11]. Other treatment options, such as prolonged antibiotic intravenous treatment in hospital have not been used (or accepted) in the management of children from remote Aboriginal communities [12, 13]. Topical quinolone antibiotics (e.g. ciprofloxacin) are currently the recommended first line treatment for CSOM and are theoretically more active against the bacteria commonly associated with CSOM (*Pseudomonas aeruginosa*), but have failed to eradicate all pathogens involved (particularly *Staphylococcus aureus*). Our previous randomised trial comparing topical treatments, ciprofloxacin versus framycetin (0.5%), gramicidin, dexamethasone (sofradex®) for CSOM found that *Staphylococcus* species were the most commonly isolated pathogens in ear discharge after treatment (present in 75% of specimens). We also documented an as overgrowth of fungal species. [9] There are no large studies describing the microbiology of CSOM in Aboriginal children. There is also lack of evidence for the effectiveness of combining antiseptic ear washes (povidone-iodine) with topical antibiotics (ciprofloxacin or sofradex®). The only randomised controlled trial (RCT) in Aboriginal children to describe a treatment that was effective in the majority of children with CSOM (around 75%) used the combination of povidone-iodine ear washes followed by ciprofloxacin ear drops. However, there were important differences in the severity of disease in these children compared to those currently living in remote communities of the NT [14]. Based on the clinical trials literature, treatment with oral antibiotics is not recommended routinely for CSOM and are usually less effective than topical antibiotic treatment. In our most recent CSOM study, 75% of children who sought clinical care from their regular health care provider were prescribed amoxycillin. It is unclear whether this oral treatment is ever indicated. [15–17] The only published placebo-controlled trial found the addition of oral cotrimoxazole to topical aminoglycoside plus steroid treatment reduced persistent discharge by 25 and 15% after 6 and 12 weeks of treatment [18]. Currently, there is a preference for surgical repair of the tympanic membrane in older children with chronic perforations that are dry at time of surgery [19]. This RCT will determine the clinical and bacteriological efficacy of oral antibiotics and povidone-iodine ear washes in addition to current recommended treatment (dry mopping plus topical antibiotic drops). Outcomes after four months, and at 12 months follow-up will include degree of resolution of ear discharge, bacterial pathogen persistence, healing of the tympanic membrane and hearing levels.

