### Ethics, consent and permissions

This study was approved and reviewed six monthly by the Human Research Ethics Committee of the Northern Territory Department of Health and the Menzies School of Health Research (HREC-2014- 2170), and the Central Australian Human Research Ethics Committee (CAHREC-14-228). The trial was conducted in accordance with the principles of Good Clinical Practice (GCP), the Declaration of Helsinki and the National Health and Medical Research Council (NHMRC) recommendations for research in Indigenous communities. Each participating community council/board provided written approval of the study to the ethics committees. Freely given informed written consent was obtained in person, by the research nurses from every subject’s parent/guardian (plus assent from children over 10 years of age) prior to enrolment. The study information, provided face-to-face in written, oral, and pictorial formats have been approved by the Ethics Committees. An interpreter was used when requested (or deemed necessary by the researchers). Sufficient time was provided to ask questions, discuss participation with relevant others, and obtain further study details prior to signing and dating consent forms. Consent included permission for their child to have an ear examination, nasal and ear swabs, a general child health check at baseline, 4 and 12 months follow-up visits. Details of data collection at each of the scheduled assessment times are summarised in Table 1. Signed consent was also sought to access their child’s medical records, complete a lifestyle interview regarding information on likely risk or protective factors for otitis media, to use the study and standard medicines, and to be contacted by study researchers at the participant’s home and via phone or social media, for the duration of the clinical trial.

**Table 1 Tab1:** Schedule of assessments

Visit #	0	1	2	3
Event	^a^Screening	Day1	16weeks	12months
Informed consent				
Check informed consent				
Randomisation^b^				
Ear exam				
Check inclusion/exclusion criteria				
Nose and ear swabs				
Lifestyle questionnaire				
Clinical note review				
Check recent audiology				
General health check				
Record antibiotic/study medication use				
SAE reporting^c^				

^a^Screening is an ear exam to assess ear status and can occur on Day 1

^b^ Randomisation may be conducted at the time of screening

^c^Severe adverse events reporting will occur throughout the study

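### The adjusted carriage analysis leaves out baseline carriage of the same organism, although baseline swabs are collected, so it may give up precision

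*Protocol article*

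**What the plan says.** All references are to the protocol article.

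- **Outcome.** The Outcome measures section lists, at 4 and 12 months, "presence of recognised bacterial pathogens in nose and ear discharge", and adds "the proportion of children with any carriage of pneumococci and any carriage of vaccine or non- vaccine serotype pneumococci and any carriage of NTHi". Both describe the state at follow-up.
- **Analysis.** The Carriage outcomes section describes carriage at 16 weeks and 12 months for each organism and then states: "A binomial regression will be used to estimate the crude and adjusted effect of the two interventions on carriage outcomes in the same manner" as for the primary outcome.
- **Adjustment set.** The Primary clinical outcomes section fixes it: "The adjustment set will comprise of the stratification factors (age group and community) and the other intervention".
- **Baseline data.** The Ethics, consent and permissions section covers consent to "nasal and ear swabs, a general child health check at baseline, 4 and 12 months follow-up visits". No section uses the baseline swabs in an analysis of effect.
- **Contrast.** The Audiology outcomes section adjusts the hearing outcome for baseline hearing by ANCOVA.
- **Stray wording.** The last sentence of the Background previews the outcomes differently: "Outcomes after four months, and at 12 months follow-up will include degree of resolution of ear discharge, bacterial pathogen persistence".

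**The concern.** The adjustment set was written for an outcome that has no useful baseline value. Every child enters with CSOM, so baseline disease status cannot separate children in the primary analysis. Carriage of a particular organism is not an entry criterion, so baseline carriage can differ between children and may predict follow-up carriage. An adjustment set borrowed unchanged therefore drops a covariate that is already collected and may be prognostic.

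At stake is the width of the confidence intervals for the adjusted carriage effects, which are secondary outcomes. There is also a smaller point of wording. Persistence, read strictly, refers to an organism found at baseline, whereas the listed and analysed outcome is presence at follow-up whatever the baseline state.

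**Working it through.** **1. The plan's own figure.** The only sample size stated is for the primary outcome: 280 children, 90% power, failure of 70% against 50%, two-sided 5%, 10% loss. With p1 = 0.70, p2 = 0.50 and mean 0.60:

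n per group = [1.96·√(2·0.60·0.40) + 1.2816·√(0.70·0.30 + 0.50·0.50)]² / 0.20² = (1.358 + 0.869)² / 0.04 ≈ 124.

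That gives 248 in total, and 248/0.90 ≈ 276 against the stated 280. With 280 × 0.90 = 252 evaluable children (126 per margin), power is 90.5%. The figure reproduces, so the sample size is not at issue. The 252 is carried forward.

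**2. Is baseline carriage in the adjusted model?** The Carriage outcomes section refers to the method for the primary outcome. That method's set has three members: age group, community and the other intervention. Baseline carriage is not among them.

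**3. What would adding it gain?** For a risk difference under linear adjustment, adding a baseline covariate multiplies the variance by about 1 − φ². Here φ is the correlation between baseline and follow-up carriage. The confidence interval width scales by √(1 − φ²), and the equivalent sample size is 252/(1 − φ²). The documents give no φ, so a range is assumed:

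| φ (assumed) | Variance reduction | CI width ratio | 252 children worth |
|---|---|---|---|
| 0.2 | 4% | 0.98 | 262 |
| 0.3 | 9% | 0.95 | 277 |
| 0.4 | 16% | 0.92 | 300 |
| 0.5 | 25% | 0.87 | 336 |
| 0.6 | 36% | 0.80 | 394 |

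**4. What such values of φ mean.** With a share b positive at baseline, persistence p among them, acquisition a among the rest, and follow-up presence y = b·p + (1 − b)·a:

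φ = (p − a)·√[b(1 − b) / (y(1 − y))].

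At b = 0.5, p = 0.60 and a = 0.40, y = 0.50 and φ = 0.20. At b = 0.5, p = 0.70 and a = 0.30, y = 0.50 and φ = 0.40. At b = 0.4, p = 0.70 and a = 0.30, y = 0.46 and φ = 0.40 × √(0.24/0.2484) = 0.39. These rates are illustrations, not figures from the documents.

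**5. Limits of the table.** φ should be read as the correlation that remains after age group and community are in the model; if those already predict carriage, the gain is smaller. It is also small for any organism that nearly all or nearly no children carry at baseline. The table covers the risk difference; no separate figure was worked out for the relative risk.

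**The case against.** **The comparison is valid as it stands.** Presence at follow-up compared between randomised groups is an unbiased intention-to-treat contrast, and adjusting for the stratification factors is sound. This stands in full; the point concerns efficiency only.

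**The wording mismatch is slight.** The sections that define and analyse the outcome agree on presence at follow-up. Persistence as an outcome occurs once, in a Background preview, and that section also reports the previous trial's microbiology as organisms isolated after treatment. This stands too: it calls for a wording edit and does not show a conflict between two defined outcomes.

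**It may be left to an unshown analysis plan.** Extra covariates for secondary outcomes often are. This stands only in part, because the article names the members of the set and applies the same method to carriage.

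**A stronger reading that a reader might infer** is that the analysis cannot answer the eradication question, and that presence has much less power than persistence among baseline carriers. The documents support neither. Absence of the organism at the end of treatment is a reasonable meaning of eradication. The power claim needs treatment to have no effect on acquisition. Take 126 per margin, 50% positive at baseline and persistence of 60% against 40%, with 63 baseline carriers per group. If acquisition is 20% in both groups, presence is 40% against 30%, and power is about 0.38 for presence and 0.61 for persistence. If acquisition also falls, from 20% to 13.3%, presence is 40% against 26.7% and power is about 0.61 for both. If it falls to 10%, the order reverses (0.72 against 0.61). Nothing in the documents says which case applies.

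**Conclusion.** The point holds as a modest one. The adjusted carriage model, as written, omits baseline carriage of the same organism although the data are collected and hearing is handled differently. There is no bias. The adjusted estimates may be less precise than the data allow, by an amount that the documents do not fix: negligible at a correlation of 0.2 or below (4% of the variance or less) and material from about 0.4 (16%). These figures rest on 252 evaluable children, a linear approximation for the risk difference, and assumed correlations.

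The reference to persistence in the Background needs aligning. It does not show that the wrong outcome is being analysed.

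**What to change.** 1. In the Carriage outcomes section, state that the adjusted models also include baseline carriage of the same organism at the same site. Keep the crude presence analysis as listed.
2. State how children without a baseline swab are handled, for example with a missing-indicator category, so that they stay in the adjusted model.
3. State a fallback in case the log or identity link model does not converge with the added covariate.
4. Either change the Background wording from persistence to presence at follow-up, or report persistence among baseline carriers as an optional descriptive supplement. Formal comparisons of both persistence and acquisition are not needed: nine carriage categories × two time points × two interventions × two measures would add 72 contrasts, many in small subsets.

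The cost is analysis wording and one more covariate. No new data are needed. The Trial status section says that data cleaning has only commenced, so the wording can be settled before analysis.
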